### **5.7.8 Data analysis and statistical methods**

The analysis of the data obtained in the randomised pilot will be performed primarily descriptively. Data will be summarised and displayed visually when appropriate. For exploration, a t-test for independent samples is used to assess whether there are differences in decisional conflict, knowledge (MCKQ) and attitude/worries towards pregnancy (MPWQ) between the two groups. The analysis of the recorded decision coaching sessions will be performed based on MAPPIN'SDM in order to assess the involvement of women with MS in the coaching session (Kasper et al., 2012).

Qualitative and quantitative data obtained in the randomised pilot phase will be analysed separately as described. For the description of the thematic analysis of the qualitative data see Data analysis and statistical methods 5.2.8. Afterwards, the data will be merged using a joint display table and discussed (Creswell & Plano Clark, 2011).

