### **5.2.3 Procedure**

The structured interview guidelines will be developed based on the results from the literature searches and other materials as for example the Australian decision aid on motherhood choice (M. Prunty et al., 2008). One interview guide will address experiences, counselling and information needs as well as concerns of women with SLE/MS to be used in focus groups and personal interviews and the other one will address physician's perception regarding motherhood in MS/SLE.

Before starting the focus group and the personal interviews, the participants have to provide informed consent and to fill a short questionnaire collecting demographic data and some specific information. Each interview will be audio-recorded and transcribed verbatim.

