### **5.7.3 Procedure**

After providing informed consent and filling in the baseline questionnaires (see 5.2.3), a study nurse of the MS outpatient clinic of the University Medical Center Hamburg-Eppendorf will

randomise eligible study participants into the two groups (1:3 allocation ratio) using block randomisation. After successful randomisation, the study nurse will provide the access to the information platform and the DST or DCP to the participating women. The participating women will be blinded as to whether they belong to the DST or DCP group.

Decision support tool: women with MS will receive the decision support tool. They will have access to the tool for two weeks and will be asked to fill in questionnaires after that period. All questionnaires will be sent by post with a stamped addressed envelope.

Decision coaching programme: 2 experienced MS nurses will be trained in the developed motherhood choice decision coaching programme. Afterwards, each nurse will provide the coaching programme for women with MS. It is intended that women will have one coaching session within two weeks after they gained access to the information platform. The coaching sessions will be audiotaped by the nurse. The women with MS will be asked to fill in questionnaires again after the decision coaching session. All questionnaires will be sent by post with a stamped addressed envelope.

At the beginning of their participation in the study, women with MS in both groups will be encouraged to make an appointment with their neurologist to discuss motherhood choice after the intervention.

After they have finished the intervention, at least 10 participants from each group will be interviewed by phone using a semi-structured interview guide addressing the feasibility. It will be addressed as well whether the topic was discussed with a neurologist. The nurses will be interviewed after they have provided the last coaching session at the end of the study. The semi-structured interviews will focus on the feasibility of the whole intervention. The randomised pilot will be conducted according to the CONSORT extension, a guidance for pilots and feasibility trials, which may be followed by a future RCT (Thabane et al., 2016).

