#### **5.7.4 Expected results**

The following outcomes will be measured in both groups. Decisional conflict (Buchholz 2011) was the primary outcome measure in the study of Prunty et al (M. C. Prunty et al., 2008) on motherhood choice in women with MS and will be applied as a key outcome measure in this project to explore possible effects. Further, knowledge (MCKQ-R) (M. C. Prunty et al., 2008) and attitude and worries towards pregnancy will be assessed (MPWQ). A process evaluation questionnaire addressing the feasibility of the intervention will be developed and women will be asked to fill in after the corresponding intervention. Here, also possible unintended consequences like anxiety towards immunotherapies are addressed. In addition, a slightly modified version of the Control Preference Scale (CPS) (Degner et al., 1997) will be included to assess the women's preferences for involvement in decisions about immunotherapies when they want to have a child.

Further, after the coaching sessions, the exploratory ratings of the extent of SDM (explored with MAPPIN'SDM) (Kasper, Hoffmann, Heesen, Köpke, & Geiger, 2012) will be conducted based on an audio-analysis. MAPPIN'SDM enables to calculate convergent validities between assessments from different perspectives (here e.g. patient, MS nurse and reviewer). Additionally, perceived SDM will be addressed in both groups by questionnaires.

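### The pilot's exploratory t-test uses no baseline score, and the cross-reference meant to define the baseline questionnaires points to a form that names none of the compared scales

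*Protocol*

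**What the plan says.** **Analysis.** Protocol section 5.7.8 states that "The analysis of the data obtained in the randomised pilot will be performed primarily descriptively". It then adds the only between-arm method named for the pilot: "For exploration, a t-test for independent samples is used to assess whether there are differences in decisional conflict, knowledge (MCKQ) and attitude/worries" towards pregnancy, compared between the two groups. It mentions no covariate and does not say whether follow-up scores or changes from baseline are compared.

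**Timing of questionnaires.** Section 5.7.3 places a first set of questionnaires before allocation: "After providing informed consent and filling in the baseline questionnaires (see 5.2.3"). For the decision support tool (DST) arm, it says of the women that "They will have access to the tool for two weeks and will be asked to fill in questionnaires after that period". For the decision coaching programme (DCP) arm it says: "The women with MS will be asked to fill in questionnaires again after the decision coaching session".

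**What the pointer leads to.** Section 5.2.3 is the procedure for the focus groups and personal interviews of step 2. Participants there are asked "to fill a short questionnaire collecting demographic data and some specific information". None of the pilot's outcome scales is named.

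**Outcomes.** Section 5.7.4 opens with "The following outcomes will be measured in both groups" and lists decisional conflict, knowledge (MCKQ-R) and attitude and worries (MPWQ) among them, without saying which are measured before randomisation. Decisional conflict "will be applied as a key outcome measure in this project to explore possible effects".

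**Size.** Section 5.7.5 gives 48 women for the DST and 16 for the DCP (two nurses with eight women each). Section 5.7.3 gives a 1:3 allocation.

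**The concern.** Two parts of the plan do not fit together. Section 5.7.3 collects something before randomisation, but the reader cannot tell what, because the reference given belongs to another study step. Section 5.7.8 then fixes a comparison that makes no stated use of baseline.

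The order matters in practice. A score not collected before randomisation cannot be recovered later, so the content of the baseline form has to be settled before enrolment. If the scales are collected, the pilot holds information on each woman's starting level that the named test does not use as a covariate. With only 16 coached women, precision is the scarce resource, and the estimated difference in decisional conflict is what the pilot offers on possible effects.

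**Working it through.** The protocol states no alpha, power, effect size, SD or baseline correlation for the pilot, so there is no sample-size calculation to reproduce. The stated arm sizes agree with each other: 2 × 8 = 16, and 48/16 = 3, which matches the 1:3 allocation.

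**Inputs.** From section 5.7.5: n = 16 and n = 48. Assumed: a 95% confidence level, equal SDs in both arms and at both time points, no missing data, and a baseline-to-follow-up correlation r of 0.3, 0.5 or 0.7.

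**1. Post-score t-test.** In SD units:
- SE = √(1/16 + 1/48) = 0.289
- t quantile with 62 df = 1.999
- 95% CI half-width = 1.999 × 0.289 = 0.577, or 0.58 SD

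**2. Baseline-adjusted model.** SE = 0.289 × √(1 − r²), with 61 df (t quantile 2.000). The equivalent total is the number of women a post-score t-test would need for the same precision, 64/(1 − r²).

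| r | √(1 − r²) | SE | Half-width | Variance reduction | Equivalent total |
|---|---|---|---|---|---|
| 0.3 | 0.954 | 0.275 | 0.55 SD | 9% | about 70 |
| 0.5 | 0.866 | 0.250 | 0.50 SD | 25% | about 85 |
| 0.7 | 0.714 | 0.206 | 0.41 SD | 51% | about 125 |

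The multiplier is the usual large-sample one and ignores the small cost of estimating the slope.

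**3. If changes from baseline were meant.** Section 5.7.8 leaves this open. For a t-test on change scores, SE = 0.289 × √(2 − 2r). This gives 0.342, 0.289 and 0.224, and half-widths of 0.68, 0.58 and 0.45 SD at r = 0.3, 0.5 and 0.7. The adjusted model is narrower in each case.

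**4. Chance imbalance.** The SE of a baseline mean difference is also 0.289 SD.
- P(|difference| > 0.3 SD) = 2 × [1 − Φ(0.3/0.289)], about 30%
- P(|difference| > 0.5 SD) = 2 × [1 − Φ(0.5/0.289)], about 8%

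An imbalance enters a post-score difference multiplied by r. An imbalance of 0.3 SD shifts it by 0.09, 0.15 or 0.21 SD at r = 0.3, 0.5 or 0.7. An imbalance of 0.5 SD shifts it by 0.15, 0.25 or 0.35 SD. This variation is already contained in the unadjusted SE of step 1.

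**The case against.** The strongest reply is that nothing here is invalid. Under randomisation the unadjusted t-test is unbiased, and chance imbalance is random error that its standard error already covers. The analysis is mainly descriptive, the test is labelled exploratory, and no power claim rests on it. At r = 0.3 the gain is slight, from 0.58 to 0.55 SD. All of this stands, and it keeps the point to one of efficiency and clarity. Covariate detail is often left to a statistical analysis plan, and none is shown here. That excuses little, because the protocol itself names the t-test and gives the wrong reference.

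A second reply is that the two halves pull apart: if the scales are not collected at baseline, there is nothing to adjust for. This also stands. The precision figures hold only if the scales are collected.

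Three stronger readings are tempting but not supported:

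- **That the outcomes are not measured at baseline at all.** A reader following the cross-reference literally might infer this. But 5.7.3 speaks of baseline questionnaires in the plural, and for the coached women uses the word *again*. A wrong section number is the likelier explanation, though the protocol never confirms it.
- **That the form in 5.2.3 is purely demographic.** It also collects further information that is not specified.
- **That 5.7.8 commits to follow-up means.** This is the natural reading, but it is not stated.

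**Conclusion.** The point holds as one of unused precision and an unfixed baseline set. The cross-reference in 5.7.3 is wrong for the pilot, and the protocol nowhere says that the three compared scales are completed before randomisation. If they are, a model with the baseline score would reduce the 95% CI half-width from 0.58 SD to between 0.55 and 0.41 SD, for assumed correlations of 0.3 to 0.7. These figures rest on the planned 16 and 48 women, equal SDs, no dropout and a post-score comparison. The correlation is an assumption, since the protocol gives none.

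A reader might go further and conclude that the t-test gives a biased or misleading result. The documents do not support that: it is a valid exploratory comparison, and a baseline imbalance affects it only in proportion to r.

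**What to change.** **Section 5.7.3.** Remove the reference to 5.2.3 and state that the three scales compared in 5.7.8 (DCS, MCKQ-R and MPWQ) are completed before randomisation.

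**Section 5.7.8.** Replace the independent-samples t-test with a linear model of the follow-up score on arm and the baseline score of the same scale. Report the adjusted mean difference with its 95% CI. This also removes the uncertainty over whether post scores or changes are compared, and an estimate with an interval suits a mainly descriptive analysis.

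**Cost.** Two short edits to the protocol and one model per scale. If the scales are not already part of the baseline set, the women fill in a longer form at a contact that already exists.

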## **5.8 Multinational web-based survey**

### **5.8.1 Study setting**

The multinational web-based survey will be conducted across different countries in cooperation with local self-help organisations. For instance, in Germany the self-help organisation 'Deutsche Multiple Sklerose Gesellschaft' (DMSG) is involved and will inform about the survey on their website. Previously, a qualitative evaluation with think-aloud will be conducted. In Germany, the qualitative evaluation will take place in the MS outpatient clinic of the University Medical Center Hamburg-Eppendorf. It is planned that the following countries will participate in the web-based study: Czech Republic, Denmark, Germany, Italy, Ireland, Netherlands, Spain and United Kingdom. The multinational survey will be performed using LimeSurvey (LimeSurvey GmbH, 2021), a widely established web-based survey tool.

### **5.8.2 Participants**

The participants for the survey and qualitative evaluation with think-aloud will be women with multiple sclerosis (MS) at child-bearing age between 18 and 45 years. Women who either have

already at least one child or who are dealing or have dealt with the issue motherhood are eligible to participate. Available internet access is mandatory for the web-based survey. Only women who indicate that they are fluent in the local national language and who have provided signed informed consent will be included.

### 5.8.3 Procedure

The qualitative evaluation with think-aloud and the web-based survey will include two questionnaires. The questionnaire on motherhood/pregnancy choice and worries (MPWQ) is designed to measure concerns, attitudes and coping strategies regarding pregnancy and motherhood. The motherhood choice knowledge questionnaire (MCKQ-R) will clarify the knowledge on MS and pregnancy. Both questionnaires were piloted in a cross-sectional study conducted primarily with women from a cohort exploring the modulation of immune function during pregnancy in MS (see 5.3 Questionnaire development and translation). The final results of piloting are currently being analysed. After this analysis, the final number of scales of the MPWQ (concerns, attitudes and/or coping strategies) will be identified. The validation of both questionnaires will be performed across Germany in cooperation with the DMSG before the multinational survey starts (see protocol 5.4 Web-based survey on page 17).

The web-based survey will consist of a demographical and disease specific section, a modified version of the Control Preference Scale (CPS) (Degner et al., 1997), followed by the MPWQ and MCKQ-R.

For the assessment of the convergent validity, the web-based survey will be included the validated Decisional Conflict Scale (DCS) (Buchholz et al. 2011) and Hospital Anxiety and Depression Scale (HADS) (Zigmond & Snaith, 1983) (See 5.3.8 Multinational web-based survey: Data analysis and statistical methods). In addition, the Pregnancy-Related Anxiety Questionnaire-Revised 2 (PRAQ-2) (Mudra et al. 2019) and the extension of the Leipzig Questionnaire of Motives to have a Child (LKM) (Ernst et al. 2020) will be included. All electronic data from the web-based surveys will be collected anonymously.

Before the multinational survey will be start, all questionnaires that are not yet existing in the right language of the local country will be translated forwards and backwards. Afterwards, they will be qualitatively evaluated with women with MS using think-aloud (Jaspers et al. 2004). Women with MS are given the two developed questionnaires (MPWQ and MCKQ-R) as well as all further translated questionnaires and asked to fill them out aloud. Thus, the the comprehensibility and user-friendliness of thes questionnaires will be assessed.

### 5.8.4 Expected results

The web-based survey will on the one hand validate the MCKQ-R and the MPWQ for the participating countries. On the other hand, the survey will be gathering the percentage of women with MS considering pregnancy as well as their worries, attitude, knowledge and decisional conflict across the different countries (explored with the MCKQ-R, DCS, and the MPWQ). Therefore, cross-country insights and differences about motherhood and MS can be identified.

Based on the results of an international study on the risk knowledge level in people with relapsing-remitting MS, we expect that the knowledge level about MS and motherhood/pregnancy will be moderate in all participating countries. Generally, we hypothesise that a higher knowledge level is associated with women who are currently considering a pregnancy or are already pregnant compared to women who have already children, because the issue of motherhood and MS is more present in these women.

Regarding the results of the MPWQ, we expect different results in each country for the possible scales attitudes, concerns as well as coping strategies. Depending on the country, there might be participants who will be more concerned or have more coping strategies in relation to participants from the other countries. In general, we assume that participants who have already had at least one child after the MS diagnosis will be less concerned, have more coping strategies and a more positive attitude towards MS and motherhood compared to childless women or women considering pregnancy.

### **5.8.5 Sample Size**

In each country, the qualitative evaluation will include at least five and the web-based survey at least 50 women with MS at the childbearing age (18-45 years) considering pregnancy in each country.

### **5.8.6 Recruitment**

The participants will be primarily recruited via local self-help organisations of the different countries. Here, flyers, websites, social media sites of the organisations as well as mailing lists will be used to inform potential participants. In addition, MS outpatient clinics will recruit participants for the qualitative evaluation and will inform about the survey.

### **5.8.7 Participant timeline**

The mean duration of the participation in the qualitative evaluation with think-aloud will take about 20 minutes and in the web-based survey about 30 minutes.

### **5.8.8 Data analysis and statistical methods**

The audio material of qualitative evaluation will be transcribed if necessary. Each participating country will evaluate its qualitative data descriptively. The pseudonymized results of the qualitative evaluation of each country will be collected in Hamburg and evaluated.

The raw data of the multinational study will be exported from the online database LimeSurvey. Data analysis will be performed with the software programme SPSS (version 24/25) and demographic data will be analysed using descriptive statistics.

The developed questionnaires (MCKQ and MPWQ) will be evaluated for their psychometric properties using standard procedures as previously described (Gold et al., MSJ 2001) and modified if necessary (see 5.3.8 Questionnaire development and translation: data analysis and statistical methods). This includes assessments of item difficulty and score distributions (floor/ceiling effects), reliability (internal consistency) and aspects of validity (construct validity and convergent validity). A detailed description can be found in the protocol (see 5.3.8 Questionnaire development and translation: data analysis and statistical methods).

Differences in MCKQ and MPWQ scores across countries will be calculated using ANOVA. A mixed model regression approach will be used to investigate the effect of independent variables, such as the score of the Patient Determined Disease Steps (PDDS) scale, age, number of children before MS diagnosis and being on disease modifying drugs, on the MCKQ and MPWQ scores.

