#### **5.3.8 Data analysis and statistical methods**

The raw data of the cross-sectional studies will be exported from the online database UNIPARK. Data analysis will be performed with the software programme SPSS (version 24/25) and demographic data will be analysed using descriptive statistics.

The newly developed questionnaires will be evaluated for their psychometric properties using standard procedures as previously described (Gold et al., MSJ 2001) and modified if necessary. This includes assessments of item difficulty and score distributions (floor/ceiling effects), reliability (internal consistency) and aspects of validity (construct validity, convergent and discriminatory validity). An item analysis is planned to determine the item difficulty, item discriminatory power and item distribution. Values between 0.20 and 0.80 are expected for the item difficulty, and the item discriminatory power should be between 0.40 and 0.70. For the determination of the internal consistency of the questionnaire, Cronbach's alpha will be calculated; hereby, for a high internal consistency of the test, the values should be above 0.70. Reproducibility over time will be assessed by Pearson product moment and intraclass correlations (ICC). Appropriateness of the questionnaires will be tested by examining score distributions and floor/ceiling percentages on each scale. In general, a percentage of less than 20% is considered satisfactory. Construct validity will be assessed by exploratory factor analysis (Bühner, 2006).

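### The multinational survey's country comparison names no covariates, although the protocol expects scores to depend on motherhood status, so uneven case-mix may appear as country differences

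*Protocol*

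**What the plan says.** Section 5.8.8 of the protocol gives the country comparison one method: "Differences in MCKQ and MPWQ scores across countries will be calculated using ANOVA". It names no covariates. The next sentence plans a second model on the same scores: "A mixed model regression approach will be used to investigate the effect of independent variables". Its examples are the Patient Determined Disease Steps (PDDS) score and "age, number of children before MS diagnosis and being on disease modifying drugs, on the MCKQ and MPWQ scores". Country is not listed, and adjusted country differences are not promised.

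Eight countries are planned (section 5.8.1): "Czech Republic, Denmark, Germany, Italy, Ireland, Netherlands, Spain and United Kingdom". Section 5.8.5 sets a minimum of 50 women in each.

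On who takes part, section 5.8.6 says: "The participants will be primarily recruited via local self-help organisations of the different countries". No quota or weighting is described. Section 5.8.2 admits women who already have a child alongside women for whom motherhood is, or has been, an open question.

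Section 5.8.4 states the intended reading: "cross-country insights and differences about motherhood and MS can be identified". The same section expects women with a child born after diagnosis to be less concerned, to have more coping strategies and to hold a more positive attitude. It also expects women who are considering pregnancy or are pregnant to know more than women who already have children.

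On comparability of the instruments, section 5.8.3 says that "all questionnaires that are not yet existing in the right language of the local country will be translated forwards and backwards", followed by think-aloud testing. For structure, section 5.8.8 refers back to section 5.3.8: "Construct validity will be assessed by exploratory factor analysis".

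**The concern.** The protocol predicts that scores depend on motherhood status and pregnancy intention, admits women of every such status, and recruits them through channels that may reach different women in each country. It then compares countries by a method for which no adjustment is named. If one country's respondents are mostly mothers and another's are mostly women still deciding, their means will differ even where women in the same situation would score the same.

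The second model does not close the gap as written. Besides not naming country, its only child variable is the number of children before diagnosis, whereas the section 5.8.4 hypotheses turn on a child after diagnosis and on current intention.

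There is a related, lesser question. The listed psychometric checks (item difficulty, floor and ceiling, internal consistency, exploratory factor analysis, convergent validity) do not test directly whether an item behaves alike in each language version.

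At stake is the interpretation of one stated result of the survey. The randomised pilot is not affected.

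**Working it through.** **The plan's own figure.** The minimum is 8 countries x 50 women = 400. No alpha, power, effect size or SD is given for it, so it cannot be re-derived. The rest is an illustration on declared assumptions.

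**Assumptions (not in the protocol).** Two-sided 5% level; within-subgroup SD of 1; one binary case-mix factor (for example, child after diagnosis) that shifts the score by *d* SD; its share *p* evenly spaced across the eight countries; no true country effect once that factor is held fixed.

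**Method.** One-way ANOVA with 8 - 1 = 7 and 400 - 8 = 392 df; the critical F is 2.03. Case-mix alone gives the noncentrality

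λ = n·d²·Σ(p_i - p̄)² / [1 + d²·mean(p_i(1 - p_i))], with n = 50.

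The largest gap between two country means is d x (highest share - lowest share).

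**Results for d = 0.5.**

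| Shares across countries | Σ(p_i - p̄)² | mean p(1 - p) | λ | Largest gap | Rejection rate |
|---|---|---|---|---|---|
| 40-60% | 0.0343 | 0.2457 | 50 x 0.25 x 0.0343 / 1.0614 = 0.40 | 0.10 SD | 6.5% |
| 30-70% | 0.1371 | 0.2329 | 50 x 0.25 x 0.1371 / 1.0582 = 1.62 | 0.20 SD | 11.7% |
| 20-80% | 0.3086 | 0.2114 | 50 x 0.25 x 0.3086 / 1.0529 = 3.66 | 0.30 SD | 22.8% |

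**Sensitivity to the assumed effect.** With d = 0.3 the three rates are 5.5%, 7.2% and 10.5%. With d = 0.8 they are 8.7%, 23.7% and 53.4%.

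**Does adjustment help?** Simulation, 4,000 runs per scenario, comparing the unadjusted country test with one that includes the case-mix factor:

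| Shares, d | Unadjusted | Adjusted |
|---|---|---|
| 50% everywhere, 0.5 | 4.4% | 4.5% |
| 30-70%, 0.5 | 12.0% | 4.9% |
| 20-80%, 0.5 | 22.0% | 5.2% |
| 20-80%, 0.8 | 53.8% | 4.4% |

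Adjusting for the factor that differs brings the rate back to about 5%. Adjusting for a different variable, such as children before diagnosis, would do so only as far as it stands in for that factor.

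**Translation.** Covariates cannot remove a shift in the instrument itself. With equal case-mix, a score shift in one country of 0.2, 0.3 or 0.5 SD gives rejection in 12%, 24% or 65% of surveys. With a 0.5 SD shift in one country and shares of 30-70% (d = 0.5), the adjusted test still rejects in 64%. The protocol gives no basis for saying how large such a shift would be, or whether there would be one.

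**The case against.** The strongest reply is that the mixed model in the next sentence may already do the work. Its covariates are examples rather than a closed list. In a one-time survey, country is the most evident grouping level for a mixed model, so it may well be a term. Model details are often left to an analysis plan, which is not at hand. This stands in part: that the comparison is unadjusted is the natural reading of section 5.8.8, not its wording. But the protocol gives country differences to the ANOVA and gives the mixed model another purpose. The factors that section 5.8.4 singles out are absent from its examples.

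Second, a difference in sample means is a legitimate description. Having a child after diagnosis may also be a consequence of worry or attitude, so adjusting for it can remove part of a real country difference. This stands, and is a reason to report both estimates.

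Third, the size is assumed throughout. At shares of 40-60% and effects of 0.3 to 0.5 SD the rate is 5.5% to 6.5%, close to nominal. This stands too.

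A reader might go further in four ways that the documents do not support:

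- **That artefacts will be reported as national differences.** This is a risk that depends on case-mix, not a certainty.
- **That translation is unchecked.** Forward and backward translation, think-aloud testing with at least five women per country, and psychometric validation for the participating countries are all planned. They reduce translation problems without ruling them out. Germany uses the source version, and Ireland and the United Kingdom could share one in English.
- **That country ranking is a headline result.** The synopsis describes this step as validation, and the objectives contain no country comparison.
- **That repeat respondents will raise German knowledge scores.** The same patient society advertises both German surveys, but no repeat rate is given and nothing says that respondents receive the answers.

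**Conclusion.** The point holds as a cheap improvement to an exploratory part of the study. The protocol names no covariates for the country comparison, and its separate regression neither names country nor lists the factors that the protocol expects to matter. With 8 x 50 women, no true country effect and an assumed 0.5 SD subgroup effect, the false-positive rate is about 7%, 11-12% or 23% for shares of 40-60%, 30-70% or 20-80%, instead of 5%. It returns to about 5% once the responsible factor is adjusted for. These figures rest on an assumed effect size, evenly spaced shares and a single binary factor, none of which the protocol gives. If the national samples are alike and the translations equivalent, the bias is negligible; the comparison as written does not show which case applies.

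**What to change.** In section 5.8.8, keep the ANOVA as a description of the sample means. Base statements about country differences on the regression already planned, with country as a fixed factor plus age, PDDS, disease modifying drugs, child before diagnosis, child after diagnosis, and current pregnancy intention. Report adjusted country differences with 95% confidence intervals next to the unadjusted ones.

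As a supporting exploratory analysis in the pooled data (about 400 women), check items for differential functioning by language version, and repeat the country comparison without flagged items. This should be a sensitivity analysis and not a pass/fail gate: with about 50 women per country, item-level decisions would be noisy.

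The cost is a few sentences, some extra programming and slightly wider intervals. If the demographic section does not already record child after diagnosis and current intention, it must. The adjusted estimate may remove part of a real country difference that acts through childbearing, which is why both are shown. Self-selection on unmeasured factors remains and should be stated as a limitation.
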